#### Secondary outcome measures

##### Intimate partner violence

Other outcomes of interest include physical and sexual IPV as reported by the married AGYW participant. To assess physical and sexual IPV, we have adapted items from the DHS Domestic Violence Module [19] (DHS module adapted from recommendations made by the WHO based on the Multi-country Study on Women’s Health and Violence against Women) [20]. To assess physical IPV, female participants are asked whether their husbands have done any of the following things ever and in the past 12 months: 1) pushed them, shaken them, or thrown something at them; 2) slapped them; 3) twisted their arms or pulled their hair; 4) hit them with a fist or with something that could hurt them; 5) kicked them, dragged them, or beaten them up; or 6) tried to choke them or burn them. If participants respond that they have experienced any of these forms of abuse events in the past 12 months, they are considered to have experienced recent physical IPV.

To assess sexual IPV, participants are asked whether their husbands have done any of the following things ever and in the past 12 months: 1) physically forced them to have sexual intercourse when they did not want to, or 2) physically forced them to perform any other sexual acts they did not want to. If participants respond that they have experienced either of these forms of sexual violence in the past 12 months, they are considered to have experienced recent sexual IPV.

##### Knowledge of contraceptive methods

This measure is constructed of 14 items covering knowledge of modern contraceptive methods and reproductive health. Items included in this measure were adapted from recommendations by USAID and Intrahealth International, and research by Frost, Lindberg, and Finer [21–23]. Multiple choice questions to be included in this construct include: 1) “How much time should a woman wait between giving birth and becoming pregnant again?” 2) “For the health of the mother and the baby, how much time should a woman wait between a miscarriage (a pregnancy that did not result in a birth) and becoming pregnancy again?” Response options for these two questions included: 1) zero to six months, 2) six months to a year, 3) one to two years, 4) more than two years, 5) you don’t know how much time she should wait. True or false questions adapted from Frost, Lindberg, and Finer [22] include: 1) “Contraceptive pills are effective even if a woman misses taking them for two or three days in a row;” 2) “After a woman stops taking contraceptive pills, it’s possible for her to get pregnant right away;” 3) “An IUD cannot be felt by a woman’s husband during sex;” 4) “An IUD can get permanently stuck in a woman’s body;” 5) “Women using an injectable contraceptive must get an injection every three months;” 6) “Using an injectable contraceptive can cause a woman to never be able to have children again;” 7) “Implants or an IUD can be removed early if a woman wants to get pregnant;” 8) “If a woman wanted to secretly delay having her next child, an IUD or injectable contraceptive could be used without anyone in her family knowing;” 9) “It’s okay to use the same condom more than once;” 10) “LAM is an effective form of delaying pregnancy even after the woman’s menstrual bleeding has returned after giving birth;” 11) “From one menstrual period to the next, are there certain days when a woman is more likely to become pregnant again;” and 12) “After the birth of a child, a woman can become pregnant before her menstrual period has returned.” Each correct response was assigned one point, with the resulting summary score ranging from 0 to 14.

##### Attitudes towards family planning

This measure consists of two items adapted from Camber Collective’s tool for segmentation of family planning clients in Niger [24] that reflect attitudes towards and acceptability of spacing and limiting births. The items are as follows: 1) “I think it is acceptable for a young wife to wait two years after having her first child to become pregnant again;” and 2) “It is acceptable for a couple to try to limit the number of children they have.” Response options for both questions were agree and disagree with one point assigned to each “agree” response. Based on their responses to these two questions, participants will be assigned a score between 0 and 2 with a higher score representing attitudes more supportive of modern contraceptive method use.

##### Perceived community norms regarding contraceptive method use

Participants are asked two questions about their perceptions of community acceptance regarding modern contraceptive method use. These items were developed to align with RMA intervention activities. The items are as follows: 1) “Men in your community think that it is acceptable for their wives to use a family planning method to delay or space pregnancies.” and 2) “People in your community think a young wife who uses a family planning method to delay or space pregnancies is not fulfilling her duty to her family.” Response options for both questions were agree and disagree with one point assigned to each “agree” response. Based on their responses, participants will each be assigned a score between 0 and 2 with a higher score representing perceived community norms more supportive of modern contraceptive method use.

##### Self-efficacy to use contraception

Participants are asked six questions to assess their self-efficacy, i.e., confidence in their ability to obtain, negotiate, and effectively use contraceptive methods. Items were adapted from recent research on this topic [25–27]. The six items are as follows: 1) “I feel confident in my ability to suggest to my husband that we wait a healthy amount of time to have another baby”, 2) “I feel confident in my ability to suggest to my husband that we use a family planning method,” 3) “I feel confident in my ability to persuade my husband to allow me to use a family planning method,” 4) “I could not continue to use a family planning method if I thought that my in-laws might find out” (reverse coded), 5) “If I wanted to use a family planning method to delay getting pregnant, I feel confident in my ability to be able to get the family planning method of my choice,” 6) “If I wanted to use a family planning method to delay getting pregnant, I feel confident in my ability to be able to use the family planning method of my choice correctly.” Response options were agree (point value = 1) and disagree (point value = 0). A summary score will be created, adding together participants’ responses and assigning participants a score of 0–6, with a higher score representing a higher level of self-efficacy.

##### Intention to use a modern contraceptive method

Intent to use a modern contraceptive method in the next three months will be assessed via a subset of the following four survey questions developed to align with RMA program goals and activities: 1) (for those currently using a modern contraceptive method - IUD, injectable, implant, pill, male condom, female condom, emergency contraception, LAM) “Will you continue to use [Current Method] over the next three months to avoid or delay pregnancy?” 2) (for those not currently using a modern contraceptive method) “Will you use a family planning method in the next three months to avoid or delay pregnancy?” 3) (for those who are currently pregnant) “After your current pregnancy is over, will you use a family planning method to space or delay pregnancy?” and 4) (if ‘yes’ to of any of the above) “Which family planning method would you prefer to use?” If participants respond that they intend to continue use for the next three months, start use in the next three months, or use after current pregnancy, and that the method that they prefer to use is considered a modern (vs. traditional) method, they will be considered as intending to use a modern contraceptive method in the next three months.

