#### Conceptual model

Adapted from Fishbein and Yzer’s modified Theory of Reasoned Action, [12] Fig. 2 depicts the conceptual model of the RMA intervention and the hypothesized pathways through which the intervention promotes change. The primary goal of the RMA intervention is to increase use of modern contraceptive methods among married adolescents age 13–19 years-old and their husbands in Niger. The RMA intervention provides education and counseling on use of modern contraceptive methods and the importance of delaying and spacing pregnancies, particularly for adolescents, alongside promotion of gender equitable attitudes towards, and norms regarding joint decision-making and use of modern contraception. Education on modern contraceptive methods, inclusive of reproductive anatomy and dispelling common misconceptions regarding contraceptives and fertility, is hypothesized to improve knowledge of, attitudes towards, and norms regarding contraceptive use. In parallel, promotion of gender equitable attitudes and norms is hypothesized to reduce perpetration of IPV. Research has demonstrated that IPV is associated with self-efficacy around SRH [13] thus, together, these elements are hypothesized to increase self-efficacy to use modern contraceptive methods. This in turn, will increase intention to use a modern contraceptive method finally resulting in actual modern contraceptive method use. Modern contraceptive methods promoted include intrauterine devices (IUD), injectable contraceptives, contraceptive implants, oral contraceptive pills, male condoms, female condoms, emergency contraception, and lactational amenorrhea (LAM).

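### Intention outcome: a current user who plans to change to another modern method, and so answers no to the item on her present method, is coded as not intending to use one

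*Protocol article*

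**What the plan says.** In the Protocol article, section *Intention to use a modern contraceptive method*, the outcome is introduced so: "Intent to use a modern contraceptive method in the next three months will be assessed via a subset of the following four survey questions". The four items are routed as follows.

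- Item 1, current modern users: "Will you continue to use [Current Method] over the next three months to avoid or delay pregnancy".
- Item 2, "for those not currently using a modern contraceptive method": whether she will use any family planning method in the next three months.
- Item 3, "for those who are currently pregnant": whether she will use a method once the pregnancy is over.
- Item 4, asked conditionally: "if ‘yes’ to of any of the above) “Which family planning method would you prefer to use".

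The coding rule has two parts. The first lists three qualifying answers, the last of them for women who are pregnant: "If participants respond that they intend to continue use for the next three months, start use in the next three months, or use after current". The second, joined by 'and', requires the method named in item 4 to be modern.

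Three other places matter. *Study overview and design* says the same data are collected in every round and lists intention among the hypotheses. *Planned analytic approach* analyses outcomes by difference-in-difference with a time by treatment interaction. *Primary outcome measure* makes current modern use the main outcome and leaves pregnant women out of its analysis; the intention outcome includes them through item 3.

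**The concern.** The outcome is about using any modern method, but for current users the question narrows to the one method in hand. A woman can truthfully answer no to item 1 and still fully intend to be using a modern method throughout the window. None of the other printed items then picks her up.

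Item 4 adds a second problem. It asks about preference ("Which family planning method would you prefer to use"), and the rule lets that preference override an intention already stated in item 1.

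Only current modern users are exposed to either error, and their number is what the intervention is meant to raise. The amount of miscoding is therefore linked to arm and to time. Intention is also the step just before use in the *Conceptual model*, so a distorted arm contrast would affect how that pathway is read.

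**Working it through.** The plan states no figure on this point, so there is none to reproduce. The main check is a trace through the printed routing; the arithmetic only indicates size.

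**1. Planned switcher (for example pill to implant) who answers no to item 1.** Item 2 is not asked, because she is a current modern user. Item 3 is not asked, because she is not pregnant. Item 4 is not asked, because there was no yes. She has no qualifying answer and is coded as not intending. The true status is intending: a false negative.

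**2. Continuing user who prefers a traditional method.** Item 1 is yes, which meets the first part of the rule. Item 4 is a traditional method, so the second part fails. She is coded as not intending. This is again a false negative, in the same direction as step 1.

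**3. Size of the error in step 1.** Inputs:

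- Use without intervention effect: 7% (*Background*, married 15–19-year-olds, 2012).
- Odds ratio on use: 2.0 (*Power*).
- Share s of current users who plan another modern method and answer no to item 1: not in the document, assumed.

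Odds at 7% = 0.07/0.93 = 0.0753. Doubled = 0.1505. Use = 0.1505/1.1505 = 13.1%.

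Miscoded share of an arm = s × use. Understatement of the difference = s × (13.1% − 7%) = s × 6.1 points.

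| s (assumed) | control | intervention | understatement |
|---|---|---|---|
| 5% | 0.35 | 0.65 | 0.3 points |
| 10% | 0.70 | 1.31 | 0.6 points |
| 20% | 1.40 | 2.62 | 1.2 points |

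If both arms start at 7% and s stays constant, the baseline error cancels in the difference-in-difference, but the error from the later rise in use does not. Because pregnant women are in the intention denominator and not in the use outcome, these figures are somewhat too high: with a pregnant share p they shrink by the factor (1 − p).

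**4. Direction.** Let s differ by arm, say 20% in control and 10% in intervention. Control loses 0.20 × 7% = 1.4 points and intervention 0.10 × 13.1% = 1.3 points. The bias vanishes or slightly reverses.

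**5. Scale against precision.** From *Power*: 240 per arm in 12 clusters gives 20 per cluster. With intra-cluster correlation 0.05, the design effect is 1 + 19 × 0.05 = 1.95, and the effective number is 240/1.95 = 123 per arm. At an assumed 30% intention, the standard error of a two-arm difference at one time point is √(2 × 0.3 × 0.7/123) = 5.8 points. A bias of 0.6 to 1.2 points is about 0.1 to 0.2 standard errors.

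**6. Would restricting the measure to non-users avoid the problem?** Suppose true intention is 20% in both arms and every current user intends. Among non-users, intention is (20 − 7)/93 = 14.0% in control and (20 − 13.1)/86.9 = 8.0% (unrounded) in intervention: a spurious −6.0 points. At 30% true intention it is 24.7% versus 19.5%, about −5.3; at 40%, 35.5% versus 31.0%, about −4.5. The restriction does more harm than the defect.

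**The case against.** The strongest reply is that the effect is small and its size assumed. No switching share is given; at 10% to 20% the distortion is a fraction of a standard error on one of several secondary outcomes. That stands, and it limits the weight of the point. It does not make the coding agree with the outcome's definition.

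Some planned switchers will answer yes to item 1, because they expect to use the present method for part of the window, and then name a different modern method in item 4. They are coded correctly. That also stands: the error covers only those who answer no.

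The article is a summary and the tablet questionnaire is not shown, so an unprinted follow-up after a no is possible. However, the article presents these four items as the source of the outcome, and none of them does this.

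Three stronger readings are tempting.

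- A reader might infer that the bias must run against the intervention. That holds only if planned switching is about equally common across arms (step 4).
- A reader might infer that users of the last two methods in the *Conceptual model* list ("emergency contraception, and lactational amenorrhea (LAM") are miscoded as a matter of course, since those methods seem hard to continue for three months. The article does not say how long they are used or how such users answer item 1, so this is conjecture.
- A reader might see the item 4 condition as an offsetting error. It is not; it also turns intenders into non-intenders.

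Finally, changing the item at 40 months alone could make the rounds non-equivalent. That is a fair warning, met by also reporting the printed coding in every round.

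**Conclusion.** The point holds on the printed routing and coding rule. A current modern user who answers no to item 1 because she plans another modern method is coded against the outcome's own definition, and so is a continuing user who prefers a traditional method. Both are false negatives confined to current modern users.

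The first error understates the intervention effect on this secondary outcome by about 0.6 to 1.2 percentage points. That rests on assumed switching shares of 10% to 20%, equal across arms and constant over time, and on use of 7% versus 13.1%. The second error cannot be sized from the document. The primary outcome is not affected. The problem is modest, but it concerns a named hypothesis and is cheap to repair while the 40-month survey is still ahead.

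**What to change.** 1. At the 40-month survey, ask current users who answer no to item 1 whether they will use any family planning method in the next three months and, if so, which one. Count a modern method as intention.
2. In all rounds, code a current modern user who answers yes to item 1 as intending, whatever she answers to item 4.
3. For the difference-in-difference, keep the all-women measure, pregnant women included. Report it with users who said no to item 1 coded both ways (all intending, none intending), and alongside the printed coding so that the rounds stay comparable. Because switching may differ by arm, coding these users in opposite ways in the two arms gives the outer limits of the contrast.
4. Do not make intention among non-users the common measure. It conditions on current use, which the intervention is meant to change, and it would also drop the pregnant women whom item 3 brings in.

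The cost is one added skip-pattern line in the tablet survey and a revised coding rule. The small downside is that values for switchers at baseline and 24 months are bounded, not exact. The share of women who are current users and answered no to item 1 sets the width of that band and can be read from data already collected.

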#### Data analysis

##### Planned analytic approach

A difference-in-difference approach utilizing multi-level, mixed-effects logistic regression models will be used to evaluate associations between intervention exposure and the primary and secondary outcomes identified above. The equivalent linear regression models will also be examined for significant findings in order to more clearly interpret results. These models will take into account the multiple study arms, cluster randomization, and repeated measurements over time. All models will include time (baseline or follow-up), treatment arm, district, and select covariates as fixed effects as well as a time by treatment interaction term. Descriptive analyses to describe the frequency of demographics and behavioral and social constructs as well as bivariate analyses to assess differences in demographics by treatment group and by loss to follow-up will be conducted. Any characteristics identified as significantly associated with treatment or female loss to follow-up at the *p* < 0.20 threshold will be considered as potential covariates (fixed effects) in adjusted models assessing effects of the intervention. Collinearity of covariates will be assessed, and highly collinear covariates may be removed from final models.

Study analyses will take into account clustering within villages using nested random effects specifications due to repeated measurements over time of individuals nested within villages. Models to assess the role of male engagement will include a three-level predictor of male participation in either household visits or small groups and include only those arms that received that intervention activity. Outcome analyses will use an intent-to-treat approach; per-protocol analyses will be conducted secondarily. Missing data on demographics and birth history will be computed where alternate data is available (e.g. calculating age from date of birth if age is not provided); however, no missing data will be imputed. All scales to be used as outcomes will be assessed for internal reliability at baseline using exploratory factor analysis and Cronbach’s alpha. If scales are multifactorial or not internally reliable, they may be modified to more accurately reflect the intended construct and/or be presented as individual item outcomes. Analyses will be conducted using STATA version 14.2® (StataCorp LLC, 2015) [28] and SAS version 9.4® (SAS Institute Inc., 2018) [29] programming applications. Trial results will be presented to the Ministry of Health of the Republic of Niger then communicated via peer review journals and scholarly meetings as well as meetings with national/international stakeholders.

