#### District randomization, village selection, and randomization

The Ministry of Health chose the Dosso region of Niger for the RMA intervention. This region has five districts from which three districts, Dosso, Doutchi, and Loga, were selected for participation. Based on the logistical challenges of providing all RMA intervention approaches in each district, each district was randomly assigned to one of the three intervention approaches (home visits alone, small groups alone, or a combination), with controls selected across all three districts. Based on power analyses (described below), the minimum number of clusters in each of the four arms was 12, requiring inclusion of 16 villages across each of the three districts (12 intervention and 4 control). Village selection and randomization followed a multi-stage process whereby eligible villages in the three districts were first identified based on the following criteria: 1) rural (i.e., not designated as a market town or city), 2) Hausa- or Zarma-speaking, 3) a minimum of 1000 inhabitants, and 4) located within 5 km of a *centre de santé intégré* (CSI) or *case de santé* (CS) health facility. There were 101 villages in Dosso, 110 in Doutchi, and 36 in Loga that met these criteria. From the eligible villages, we then stratified villages based on three level of health service provision: 1) villages with CSIs, larger health facilities serving multiple villages where doctors, nurses, and midwives provide the full contraceptive method mix and related counseling; 2) villages with CSs, village-level facilities where community health agents provide a subset of contraceptive methods; and 3) villages with neither CSI nor CS. Among the 247 total eligible villages across the three districts, 21% had a CSI, 56% had a CS, and 23% had neither. In order to select a sample of villages within each district that was representative of the distribution of health facilities across the region, we randomly selected nine villages with a CS, three with a CSI, and four with neither in each of the three districts. To create a control arm representative of villages in each district, and that included representation of all levels of health facility, we randomly assigned four of the total 16 villages per district to the control condition, consisting of two villages with a CS, 1 with a CSI, and 1 with neither. The remaining 12 villages were assigned to the intervention condition assigned to that district (see Fig. 3).

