#### Power

Power calculations for our study were conducted a priori based on our primary outcome of interest, modern contraceptive method use (reported by the adolescent wives in our sample). We used pairwise tests for time by treatment effects comparing each intervention group individually to the control group. We chose to account for a moderate intra-cluster correlation coefficient – kappa = 0.05 and an attrition rate of 10%. We also chose to account for the ability to detect an effect size of 2.0 greater odds of contraceptive method use, based on literature reviews of evaluations of interventions seeking to improve contraceptive use, as well as our own experience conducting such trials in other regions. Four arms with 12 clusters nested within each arm, and a sample size of 240 couples per arm (300 couples at baseline with 20% expected attrition; 1200 total baseline participating couples) was calculated to provide 80% power to detect associations of this magnitude.

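### Each intervention arm lies wholly in one district and the model has no district-by-time term, so each arm's effect includes its district's departure from the average trend

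*Protocol article*

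**What the plan says.** The protocol article's section on district randomization and village selection says that "each district was randomly assigned to one of the three intervention approaches", "with controls selected across all three districts". The layout per district follows from "requiring inclusion of 16 villages across each of the three districts (12 intervention and 4 control" villages. Villages were therefore randomised only between their own district's intervention and control.

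The Power section plans "pairwise tests for time by treatment effects comparing each intervention group individually to the control group", that is, against one control group pooled over the three districts.

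The Planned analytic approach states that all models will include time, "treatment arm, district, and select covariates as fixed effects as well as a time by treatment interaction term". Covariates picked by the screening rule also enter as fixed effects, not as interactions with time. Clustering is to be handled by "nested random effects specifications due to repeated measurements over time of individuals nested within villages".

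**The concern.** A district main effect adjusts for differences in level, which a before-after contrast removes anyway. It does not adjust for districts that change at different rates. Contraceptive supply, staffing or other programmes could move one district between 2016 and 2018 or 2019 whatever the intervention does. Because a given approach exists in only one district, such a movement enters that arm's time-by-treatment effect. A district's outside change could then be reported as an effect of household visits, small groups or both, and the Discussion says that the results will inform the Ministry of Health's scaling decisions.

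There is a second, conditional issue. If the nested random effects are intercepts for village and person only, they largely drop out of the before-after contrast. Variation between villages in how much they change would then be missing from the standard error.

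**Working it through.** **The plan's own figure.** The 80% power statement cannot be reproduced, because the control rate, alpha and sidedness are not given. With ICC 0.05 and 240/12 = 20 couples per village, the design effect is 1 + 19 × 0.05 = 1.95. A two-proportion calculation for OR 2.0 with 240 per arm then gives 35% two-sided power at a 7% control rate (the Background figure for 2012) and peaks at about 77%, at a 40% control rate. The point below does not depend on the 80%.

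**District trends.** Inputs: 3 districts, each with 12 intervention and 4 control villages (48 in all). Let d1, d2 and d3 be the district trends without any intervention.

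- Change expected in the arm of district 1: d1 + effect.
- Change expected in the pooled controls: (d1 + d2 + d3)/3.
- Difference: effect + (2/3)d1 − (1/3)d2 − (1/3)d3.

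Least squares on the 48-village layout gives the same loadings: +0.667 for the arm's own district and −0.333 for each other. If d1 = d2 = d3, the bias is zero.

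On the log-odds scale, with an outside trend in one district only (sizes assumed; the document gives none):

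| Outside OR in one district | Spurious OR, that arm | Spurious OR, other two arms |
|---|---|---|
| 1.25 | exp(0.223 × 2/3) = 1.16 | exp(−0.223/3) = 0.93 |
| 1.5 | exp(0.405 × 2/3) = 1.31 | exp(−0.405/3) = 0.87 |
| 2.0 | exp(0.693 × 2/3) = 1.59 | exp(−0.693/3) = 0.79 |

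In percentage points, an assumed gap of 5 points between one district and the mean of the others gives 5 × 2/3 = 3.3 points of bias. OR 2.0 from 7% means 13.1%, an effect of 6.1 points, so the bias is 55% of it.

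Simulated false-positive rates for the arm in the affected district (logistic-normal data, 20 women per village, ICC 0.05, village autocorrelation 0.8, tested on linear changes as an approximation to the mixed logistic model) at outside ORs of 1.25 / 1.5 / 2.0:

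- 7% use: 8% / 14% / 31%
- 15% use: 10% / 20% / 43%

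**With district-by-time added.** The fixed part is estimable (rank 6 of 6), and every district-trend loading on every arm effect is 0. At an outside OR of 1.5 the simulated false-positive rate, tested on village means, falls to about 7% (7% use) and 6% (15% use). The variance factor goes from 1/12 + 1/12 = 0.167 to 1/12 + 1/4 = 0.333, so the standard error is √2 = 1.41 times larger.

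**Village-by-time variation.** Take total variance 1, ICC 0.05, m = 20, village autocorrelation r and within-person correlation w (r and w assumed). Put vt = 0.05(1 − r) and ve = 0.95(1 − w). If the village-by-time term is left out,

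true SE / reported SE = √[(2vt + 2ve/m) / (2(ve + vt)/m)].

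For r = 0.8 and w = 0.3: √(0.0865/0.0675) = 1.13. Over w = 0.3 to 0.5:

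| r | SE ratio | Type I error, continuous formula | Type I error, binary simulation |
|---|---|---|---|
| 1 | 1.00 | 5% | not run |
| 0.8 | 1.13-1.18 | 8-10% | about 5-7% |
| 0.5 | 1.30-1.40 | 13-16% | about 6-8% |

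The binary results depend on the scale of the ICC, which the Power section does not state. With an ICC near 0.045 on the observed scale, a further simulation gave about 7.5% at r = 0.8 and 10.5-11% at r = 0.5.

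**Power for OR 2.0** (simulated, r = 0.8, no district trend):

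| Use in controls | Planned model | + village-by-time | + both terms |
|---|---|---|---|
| 7% | 50% | 44% | 23% |
| 15% | 72% | 66% | 36% |

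**The case against.** **The article is condensed, and an analysis plan may say more.** For the district term this does not help: the article says what all models will include, and time by treatment is the only time interaction listed. For the random effects it does stand. A reader might infer that the intervals are certainly too narrow, but the text neither limits the random effects to intercepts nor excludes a village-by-time term, and it gives no autocorrelation.

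**Controls are spread over all districts by design.** This stands in part. A reader might infer that arm and district are wholly confounded, or that an arm absorbs its district's whole trend. Neither is so. The control arm spans all three districts, a common trend cancels, and only the departure from the average remains. The same feature makes the district-by-time term estimable.

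**Districts were randomised.** With three districts and three approaches, bias averages to zero only over hypothetical reassignments. The one assignment made carries whatever bias it carries, and the model's standard error does not include it.

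**Nothing shows that district trends differ.** True. The sizes above are illustrations, not estimates.

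**The repair is expensive.** True. The article gives a logistical reason for one approach per district. Making the within-district contrast the only primary analysis would roughly halve power, from 44% to 23% or from 66% to 36%. Which model should lead is a judgement between bias and variance, and the document does not settle it.

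**Conclusion.** The point holds in this form. Under the stated model, each intervention arm's effect includes two-thirds of the gap between its district's trend and the mean of the other two, and the pooled-control comparison is protected only if district trends are equal. An assumed 1.5-fold outside rise in one district yields spurious odds ratios of about 1.31 and 0.87. This affects the primary outcome and every secondary outcome analysed with these models.

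The standard-error part is conditional on village and person intercepts only. Type I error then can exceed 5%: about 5-8% in most binary-outcome simulations at autocorrelation 0.8 to 0.5, higher under the continuous approximation, with no inflation at autocorrelation 1.

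The figures assume 48 equally weighted villages with 20 women each. One village withdrew after baseline and women pregnant at survey are excluded from the primary outcome, so the actual loadings will shift and the numbers will be smaller. Severity: should-fix.

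**What to change.** 1. Pre-specify a model with district-by-time fixed effects, so that each arm is compared with the concurrent control villages of its own district. Report it beside the pooled-control model for every outcome.
2. State that the pooled-control model assumes equal trends in the three districts. Do not attribute an arm effect to the intervention approach unless the within-district estimate is consistent with it.
3. Add a village-by-time random effect to both models.

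Cost: no new data are needed, only two model terms and a revised power statement. That statement should say that the within-district contrast rests on 12 versus 4 villages, with a standard error about 1.41 times larger and simulated power for OR 2.0 of about 23% at 7% use and 36% at 15% use. It should also say that the village-by-time term alone lowers simulated power by about 6 points.
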